# 3.0 Study Design

## 3.1 Overall Design

The study is a Phase 1 dose-escalating clinical trial in healthy adult malaria-naïve volunteers designed to evaluate the safety and immunogenicity of the MSP2-C1/ ISA720 malaria vaccine.

Volunteers will be recruited, and after providing written informed consent, will undergo eligibility screening, including medical history, physical examination, laboratory investigations including haematology testing, liver and renal function tests, pregnancy (females only), HIV, Hepatitis B and C screening and urinalysis. Those determined to be eligible, based on the inclusion and exclusion criteria described in **Section 4** in this protocol will be enrolled and randomised into the study. Participants will receive one of two dose regimens of the MSP2-C1/ISA720 vaccine or ISA720 as a control. Serum pregnancy tests will be performed on female volunteers of child bearing potential prior to enrollment and urine pregnancy testing prior to each vaccination; these females will be counselled to avoid becoming pregnant during the study. Clinically significant abnormalities will be reviewed by the investigators and referral for follow-up care will be provided as indicated. For eligible participants, the Day 0 visit will be scheduled for receipt of the first vaccination. Vaccinated volunteers will be observed for immediate reactions following each vaccination for 30 minutes. Volunteers will return to the clinic on Days 3, 7, 14 and 28 following each vaccination for clinical assessment, and will be given diary cards to record and grade local and systemic signs and symptoms. Phone contact will be made on D1 & D21 following each vaccination. Volunteers will also return 56 days following vaccinations 1 and 2 for screening prior to each subsequent vaccination. See **Appendix 1 Schedule of Assessments, and Table 1** for a tabular description of the vaccination schedule.

Thirty volunteers will be enrolled and assigned to one of two dose groups (10 or 40µg) or ISA720 Control as outlined in **Table 1**. All vaccines and the ISA720 Control will contain the same amount of Montanide® ISA720. As with other recombinant protein vaccines, hypersensitivity reactions would be expected to occur within the first 24 hours after receipt of the vaccine, and other severe local or systemic reactions within 72 hours. As outlined above, delayed local reactions have been observed in previous ISA720 vaccine studies. Thus, volunteers will be reviewed on days 3, 7, 14 and 28 following each vaccination, and vaccinations will be staggered within the higher dose cohort such that 5 volunteers will be vaccinated 4 weeks prior to the remaining 10 volunteers. Stopping rules as detailed in **Section 7.5** below will be in place to enable suspending the trial until review by the safety monitoring committee (SMC).

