## 1.2 Secondary Objectives

### 1.2.1. Characterise the humoral and cellular immune responses to the MSP2-C1/ISA720 vaccine

### Determine the vaccine dose level that induces the highest serum IgG concentration to MSP2 by ELISA

Table 1: MSP2-C1/ISA720 Vaccine Dose Escalation Schedule

| Time  (Week) | Cohort 1: (n = 15) | Cohort 2: (n = 15) |
| --- | --- | --- |
| 10 μg MSP2-C1/ISA720 | 40 μg MSP2-C1/ISA720 |
| 0 | Vaccination 1 (n=15) |  |
| 4 |  | Vaccination 1 (n=5) |
| 8 |  | Vaccination 1 (n=10) |
| 11 | SMC | SMC |
| 12 | Vaccination 2 (n=15) |  |
| 13 |  |  |
| 16 |  | Vaccination 2 (n=5) |
| 17 |  |  |
| 20 |  | Vaccination 2 (n=10) |
| 24 | Vaccination 3 (n=15) | SMC |
| 25 |  |  |
| 28 |  | Vaccination 3 (n=5) |
| 29 |  |  |
| 32 |  | Vaccination 3 (n=10) |
| 36 |  | SMC |
| 37 |  |  |
| 41 |  |  |
| 48 | Last Visit |  |
| 52 |  | Last visit (n=5) |
| 56 |  | Last visit (n=10) |

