**** Table 1- Timing of vaccinations shown as a minimum. First Vaccinations may be delayed.**

# 2.0 Introduction

## 2.1 Background

The World Health Organisation reported in 2005 that malaria kills more than 1 million people annually and that approximately 3.2 million people living in 107 countries or territories are at risk of infection [1]. Most of the malaria mortality occurs in sub‑Saharan Africa and in children under 5 years of age. Of the four species of malaria parasite that infect humans, *Plasmodium falciparum* is responsible for the majority of these deaths. Mounting drug resistance of the malaria parasite, as well as widespread resistance of mosquitoes to insecticides, make these control strategies increasingly unrealistic. A vaccine that would reduce both mortality and morbidity secondary to *P. falciparum* infection would be a valuable resource in the fight against this disease.

*P. falciparum* has a complex life cycle. Sporozoites, the infectious stage of the parasite, are transmitted to humans through the saliva of infected female mosquitoes while taking a blood meal. Sporozoites travel through the bloodstream to the liver, where they invade hepatocytes and then multiply asexually into merozoites. Six to 10 days after invasion, the hepatocytes rupture, releasing thousands of merozoites into the bloodstream. These merozoites invade erythrocytes, multiply and after 2 days, release progeny merozoites, which subsequently invade new erythrocytes to continue the asexual blood-stage cycle. Clinical symptoms in humans are due to this asexual blood-stage of the parasite’s life cycle. A small percentage of merozoites do not multiply after invading erythrocytes, but instead differentiate into gametocytes. These gametocytes are ingested by a female mosquito during a subsequent blood meal and undergo sexual reproduction in the mosquito midgut, producing a zygote. The zygote matures and releases sporozoites that migrate to the mosquito’s salivary glands, thus completing the life cycle.

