The most common adverse event observed in trials using Montanide ISA720 is local reactogenicity (34). The acute reactions are characterized by of pain, swelling, induration, sterile abscess, and granuloma formation. These have been generally mild to moderate in 33 to 91% of volunteers. In the single Phase 2 trial in children in an endemic area the rate was 12% (26). The overall rate for mild and moderate acute local reactions is similar to that observed with licensed pediatric vaccines such as DT (standard pediatric dose) (55% mild/moderate local reactions) or dT (low dose vaccine) (52% mild/moderate reactions) in 6-year-old children. Severe local reactions occurred only with 5 vaccinees who received the vaccine via the intramuscular route for a cumulative rate of 1%. This proportion is not greater than that observed for some licensed vaccines (17% severe local reactions with DT and 11% severe local reactions with dT) (35). Severe local reactions were seen much more commonly in trials administering the vaccine subcutaneously. In these 2 trials (30) up to 44% of recipients of higher doses were not revaccinated due to local reactions. Acute local reactions were seen frequently with pain, swelling and/or induration most common. In the HIV vaccine study (33) sterile abscess and granuloma formation was seen in some volunteers, particularly those receiving the high antigen dose (2 mg), which was far in excess of that given in the malaria vaccine studies or that planned in this study. In most studies the vaccine was injected intramuscularly and when this route was used the majority of local reactions were mild to moderate with a cumulative rate of 1% for severe reactions. In contrast, severe local reactions were seen more commonly in the two studies in which the vaccine was administered subcutaneously (31, 32).

Delayed local reactions as seen in the Combination B studies (see Section 2.3.2) occurred in some volunteers in the majority of other trials with antigens formulated in Montanide® ISA720. Over all of the studies approximately 11% of volunteers developed these reactions, which were characterized by pain and swelling at the injection site occurring 10-28 days after vaccination. They resolved without sequelae usually in a few days but in some cases several weeks. There was a trend indicating that the rate and severity of these delayed reactions was increased with higher antigen doses and multiple injections.

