## 3.3 Group Allocation, Randomisation and Blinding

The two dose groups will be screened and enrolled consecutively. Once screening has started and the first 15 participants have been deemed eligible, they will be assigned to Cohort 1 and a Day 0 visit will be scheduled. Alternates may also be identified and held in reserve. The first dose group will be vaccinated over the course of 1-2 days, with 2 participants completed a day prior to the remaining 13. If the alternates are not vaccinated, they will be invited to participate as members of the second cohort. The second dose cohort will be split into 2 subgroups for vaccination. The first 5 participants of the 40 µg dose cohort will be vaccinated at least 4 weeks after the last vaccination of the previous dose cohort and the remaining 10 participants in this dose cohort will be vaccinated at least 4 weeks after the first 4 participants in their cohort to maximize safety. After the first vaccination for each dose cohort, no replacement volunteers will be added if a subject withdraws from the study.

In this trial, everyone will be blinded to the randomisation scheme except for the study pharmacist (or designee) who prepares the vaccine dose for administration. Randomization and blinding occur within each dose cohort. The study pharmacist/nominee will prepare identical syringes containing the study vaccines, according to a randomisation schedule provided by the study statistician, so that personnel who perform the study assessments do not know the identity of the study vaccine. Each participant considered eligible for vaccination will be assigned a randomisation number at Visit 1 (Day 0) (Section 6.4). The randomization number will used to identify the participant throughout the remainder of the study.

The volume of vaccine and ISA720 Control will be identical for each group. The study pharmacist will provide the person administering vaccine with the subject’s randomisation number, initials, and a blinded syringe containing the study medication. The pharmacist (or designee) will not inform any of the investigational staff of the treatment assignment and will not perform any other subject-related duties.

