## 4.5 Indications for Deferral of Vaccination

The adverse events (AEs) outlined below constitute grounds for deferral of vaccine administration at that point in time. If any one of these AEs occurs at the time scheduled for vaccination, the participant may be vaccinated at a later date, within the allowable time interval specified in **Section 6.4** of this protocol, or withdrawn at the discretion of the investigator. The participant must be followed until resolution of the event as with any AE. If the participant is withdrawn from the study and has received at least one vaccine dose, he/she will be encouraged to remain in the safety evaluation for the duration of the study.

1. Oral temperature >37.5 °C will warrant deferral of immunisation until fever and causative illness resolve, in the opinion of the investigator.
2. Any other acute condition that in the opinion of the investigator poses a threat to the individual if immunized, or that may complicate interpretation of the safety of the vaccine following immunisation.
3. Such individual(s) will be followed by the investigators until the symptoms resolve or the window for immunisation expires. No further vaccination will be performed if the participant does not recover (oral temperature 37.5 °C and/or lack of symptoms) within the originally scheduled vaccination time interval. If the subject has received at least one dose of vaccine, he/she will be followed for evaluation of safety and immunogenicity. If the individual meets any of the above criteria for deferral on the day of first immunisation, as an alternative to deferral of vaccination, the investigator may instead elect to exclude the volunteer from further participation in the study. Eligible alternate(s) will then be vaccinated instead.

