1. Medical Investigator to perform medical history and physical examination including examination of injection site, emphasising examination of any acute complaints and targetted history taking to elicit symptoms of muscle damage (myositis), as well as exercise history, emphasizing changes in pattern of regular exercise.

2. Record vital signs.

3. Obtain approximately 14 mL of blood for haematology (FBC and differential), and biochemistry (creatinine, liver function tests, CPK).

4. Collect Days 7-13 diary card and review completion. Refer any complaints to Medical Investigator for assessment.

5. Distribute Days 14-27 diary card.

6. Record adverse events and concomitant medications.

Study Day 105 +/- 3 (Phone call ONLY)
1. Phone call to inquire about diary card entries and injection site reactions since last visit.

Study Day 112 +/- 5 (28 days after SECOND vaccination, visit 11)

1. Study staff to perform targeted history and examine injection site, emphasising examination of any acute complaints, with review by the medical investigator if required.
2. Record vital signs.
3. Collect Days 14-27 diary card and review completion. Refer any complaints to Medical Investigator for assessment.
4. Obtain 55 ml of blood for collection of blood for humoral immunity studies by anti-MSP2 ELISA, GIA and IFA, and PBMC and serum for study of cell mediated immunity.
5. Record adverse events and concomitant medications.

Study Day 140 +/- 7 (56 days after SECOND vaccination, visit 12)

1. Medical Investigator to perform medical history and physical examination including examination of injection site, emphasising examination of any acute complaints, to assess continued eligibility.

2. Record vital signs.

3. Obtain approximately 9 mL of blood for haematology (FBC and differential), and biochemistry (creatinine, liver function tests).

4. Record adverse events and concomitant medications.

Study Day 168 +/- 7 (**THIRD VACCINATION, visit 13**)

1. Medical Investigator to perform medical history and physical examination, to assess continued
eligibility to enter treatment phase.

2. Obtain approximately 24 mL of blood for haematology, (FBC and differential), biochemistry (creatinine, liver function tests CPK), and humoral immunity studies by anti-MSP2 ELISA.

3. For females, obtain a urine sample for -hCG testing. Ensure that test is negative before vaccinating; a positive test will exclude the volunteer from the trial.

4. Record vital signs.

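### The 4-week stagger in the 40 µg cohort is planned at every dose but not guaranteed at doses 2 and 3, and section 3.3 counts it from four volunteers instead of five

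*Protocol*

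**What the plan says.** Section 3.1 notes that delayed local reactions occurred in earlier ISA720 studies and concludes that "vaccinations will be staggered within the higher dose cohort such that 5 volunteers will be vaccinated 4 weeks prior to the remaining 10 volunteers". The wording is not limited to the first dose. Table 1 shows the same spacing each time: weeks 4 and 8, 16 and 20, 28 and 32. The note under the table reads "Timing of vaccinations shown as a minimum. First Vaccinations may be delayed".

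Section 6.4 gives each volunteer's dosing days as Day 84 ± 7 for dose 2 and "Study Day 168 +/- 7" for dose 3. Under section 4.5, if a reason for deferral exists on the day, "the participant may be vaccinated at a later date, within the allowable time interval specified in" section 6.4. It adds that "No further vaccination will be performed if the participant does not recover" inside that interval.

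Section 3.3 states the stagger as a minimum: "the remaining 10 participants in this dose cohort will be vaccinated at least 4 weeks after the first 4 participants in their cohort". Table 1 and section 3.1 put five volunteers in that first subgroup.

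Section 2.3.3 describes the delayed reactions as "pain and swelling at the injection site occurring 10-28 days after vaccination". It puts them at about 11% of volunteers over all studies, with a trend to more frequent and more severe reactions at higher antigen doses and with repeated injections.

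**The concern.** The stagger exists so that a delayed reaction in the first five can be seen before ten more volunteers are injected. By section 2.3.3 it should matter most at doses 2 and 3 of 40 µg, which combine the higher dose with repeat injection. Yet the windows at those doses are set volunteer by volunteer. Nothing ties the ten to the date on which the first five actually received the same dose, so a site can follow section 6.4 and shorten the gap without noticing.

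A reaction seen in time can change conduct. Section 7.2.3 treats all local reactions as causally related. Section 7.5 suspends vaccination for one Grade 3 clinical event that is probably or definitely related, except isolated Grade 3 erythema or swelling. A hold protects only those not yet injected, and Table 1 has no safety committee meeting between the two subgroups at either dose (meetings are at weeks 11, 24 and 36).

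The count of four in section 3.3 is a separate error in a safety rule. As written, the fifth volunteer falls outside the dose-1 minimum.

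**Working it through.** **Planned gap.** Table 1 gives (8 − 4), (20 − 16) and (32 − 28) weeks, which is 28 days at each dose. In trial days the first five are due on 28, 112 and 196, and the ten on 56, 140 and 224.

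**Gap allowed by the section 6.4 windows**, read as running from each volunteer's Day 0, with first doses exactly 28 days apart:

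- Dose 2 windows: first five 105 to 119, ten 133 to 147.
- One of the first five at +7, ten on schedule: 140 − 119 = 21 days.
- First five on schedule, ten at −7: 133 − 112 = 21 days.
- First five at +7, ten at −7: 133 − 119 = 14 days.
- Dose 3 windows are 189 to 203 and 217 to 231, with the same gaps.

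In general, with first doses S days apart, the smallest gap is S − 14, or S − 7 if only one side uses its window.

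**If the Table 1 weeks bind as minimums.** With first doses on time, the ten cannot be given dose 2 before day 140. A first-five volunteer at +7 still leaves 21 days, because a late dose breaches no minimum. If all first doses slip by a week, the dose 2 targets are 119 and 147. The ten may then be dosed from day 140 and the first five as late as day 126, which again leaves 14 days.

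**What is outstanding.** At 21 days, the Day 28 visit and the last week of the third diary are outstanding for the late volunteer. At 14 days, the whole third diary is outstanding, and perhaps the Day 14 ± 2 visit.

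**Illustrative chance of seeing at least one delayed reaction, of any grade, before the ten are dosed.** Assumptions: four of the first five receive vaccine; the 11% per-volunteer rate applies per dose (5% also shown); onset is even over days 10 to 28. The protocol gives neither a per-dose rate nor an onset distribution. By day 21, 11/18 = 0.611 of reactions have begun; by day 14, 4/18 = 0.222. At 11%, one recipient shows no reaction with probability 0.89 by day 28, 1 − 0.11 × 0.611 = 0.9328 by day 21, and 1 − 0.11 × 0.222 = 0.9756 by day 14.

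| Case | Formula at 11% | 11% | 5% |
|---|---|---|---|
| Full 28 days | 1 − 0.89⁴ | 0.37 | 0.19 |
| One of four at +7, ten on schedule | 1 − 0.9328 × 0.89³ | 0.34 | 0.17 |
| None late, ten at −7 | 1 − 0.9328⁴ | 0.24 | 0.12 |
| One of four at +7, ten at −7 | 1 − 0.9756 × 0.9328³ | 0.21 | 0.10 |
| All at +7, ten at −7 | 1 − 0.9756⁴ | 0.09 | 0.04 |

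Averaging over the number vaccinated among the first five (12 of 15 in the cohort) hardly moves the 11% column: 0.370, 0.340, 0.242, 0.207 and 0.094.

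**Can both rules be met?** The latest dose 2 for the first five is day 28 + 91 = 119. Adding 28 gives 147, which is Day 91 for the ten (56 + 91). So a 28-day floor always fits, provided the dose-1 gap is counted from the fifth volunteer. If that volunteer's first dose lags by k days, as section 3.3 allows, the floor can fall on Day 91 + k, outside the window.

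**The case against.** The plan does carry the stagger forward. Section 3.1 is general, Table 1 schedules it at every dose, and its note calls the timings minimums. A careful site could honour both the windows and the gap. A reader might infer from section 6.4 that the stagger lapses after dose 1; the documents do not support that. What is missing is a statement of which rule prevails. Section 3.3 does not supply one: it reads most naturally as a rule for first vaccinations, counts from the wrong number, and says nothing about the windows.

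Other safeguards exist. There is a call about injection-site reactions at Day 21 ± 3 after each dose, a clinician is reachable at all hours, the hold criteria apply throughout, and the committee meets before the first five receive doses 2 and 3. The lack of a meeting between subgroups applies equally at dose 1. The Day 28 visit has its own ± 5 days, so it can be outstanding even at a full 28-day gap. All of this stands and reduces the harm.

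Even onset may also overstate the loss. The individually dated delayed reactions in sections 2.3.2 and 2.3.3 began at 10 days, 12 days and two weeks, and one mass appeared at six weeks, which a 28-day gap would miss too. These cases are few and selected, but none falls between days 15 and 28.

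Finally, the remedy narrows the dosing window for ten volunteers to recover about 0.03 in the likeliest case. That is a real cost, set out with the fix.

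**Conclusion.** The point holds in a limited form. The 28-day stagger is planned at all three doses but not guaranteed at doses 2 and 3. One volunteer among the first five dosed at +7 brings the gap to 21 days, inside the stated onset period.

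A reader might take 14 days, or the 0.09 detection figure, as the expected position. Neither is. Fourteen days needs opposite window extremes and either section 6.4 overriding the Table 1 minimum or a slip in first doses. The 0.09 figure further needs every vaccine recipient in the first five to be late.

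The likeliest lapse has a small effect (0.37 to 0.34); dosing the ten early would cost more (0.24). These probabilities are illustrative, because the per-dose rate and even onset are assumed. They describe seeing a reaction of any grade, not triggering a hold. The day counts rest on windows running from each volunteer's own Day 0, as the study-day numbering implies.

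The count of four in section 3.3 is wrong as written, whatever view is taken of the windows. Together these warrant a clarifying amendment; they are not a serious design flaw.

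**What to change.** In section 3.3, change the count from four participants to five.

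In section 6.4, at Day 84 and at Day 168, add: *Within cohort 2, the remaining 10 receive this dose within their ±7-day window, but no earlier than 28 days after the last of the first 5 who received the same dose number.* A first-five volunteer who does not receive that dose is then not counted. No floor between cohort 1 and cohort 2 is proposed.

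The change needs no extra visits, blood or volunteers. Its cost is scheduling room. If first doses were exactly 28 days apart and the last of the first five is dosed d days late, the ten may be dosed from Day 84 + d to Day 91 (or the same days after Day 84 for dose 3). That is 8 − d days instead of 15: 8 at d = 0, 5 at d = 3 and 1 at d = 7. A deferral on that last day forfeits the dose under section 4.5.

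Starting the ten 35 days after the first five, which the Table 1 note already permits, keeps 15 − d days (8 at d = 7) and adds one week to the 56-week trial.
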